**Planning meetings**					
1)	Identified a QI program champion				
2)	Identified implementers				
3)	Completed assessment & planning meetings				
4)	Developed QI protocol based on assessment & planning meetings				
**Stakeholder meetings**					
5)	Actively participated on stakeholder meetings				
6)	Consensus on QI protocol and CMMI reviewed				
7)	Plan for QI check-ins and communication made				
**Staff training**					
8)	Staff training completed if required				
9)	Staff express readiness to start QI protocol				

*Adapted from (47)*.

### Task 4 – Measurement of the Impact of the Peer Planning and Technical Assistance Approach

A mixed-method process and outcome evaluation study will examine the implementation of the overall QI intervention and the QI protocol at each bridge organization as well as the global Accountable Health Communities (AHC) Model navigation implementation. The evaluation will have two layers to assess implementation fidelity, process, and outcomes for both the QI intervention and each QI protocol delivered at each bridge organization.

#### Evaluation of the QI Intervention

The evaluation of the QI intervention will be conducted by evaluators not directly involved in the delivery of the QI intervention. Process evaluation will assess implementation fidelity, and perceptions of those delivering and receiving the QI protocol. Implementation fidelity refers to the extent to which the planned QI protocol and revised standard operating procedures are implemented as planned. For the process evaluation, data will be collected in document review and semi-structured interviews with staff responsible for implementing the QI intervention. The evaluator will review the QI protocol, revised standard operating procedures, and navigation milestone quarterly reports submitted to CMMI and any other relevant QI documents. Coupled with the document review, semi-structured interviews with staff will be conducted to establish the current activities. Staff interviews will also assess the perceptions of the peer planning approach and QI protocol implementation. The staff interviews will be guided by the CFIR constructs used in Task 1 in order to assess staff perceptions and experiences of the QI process.

For the outcome evaluation, the methods and analysis of the document review and semi-structured interviews will reflect methods outlined in Task 1. Semi-structured interviews with the protocol staff will be used to assess progress toward intended outcomes of the QI intervention (e.g., staff satisfaction, increased self-efficacy in QI delivery). A keyword thematic analysis will be conducted to develop common themes to compare planned and current AHC activities. The themes will be considered in terms of their relationships to one another within the QI intervention and AHC navigation implementation. The evaluation team will create a coding structure to develop common themes in order to compare planned and current activities in addition to perceptions of peer planning, AHC navigation implementation, and QI protocol, as appropriate. A modified conceptual framework for implementation fidelity will be used to identify potential moderators (e.g., recruitment, participant responsiveness, comprehensiveness of policy description) to successful implementation (48). The outcomes from the QI protocols (described below) will also be used as metrics of success for the larger QI intervention.

#### Evaluation of the QI Protocols

The evaluation of the QI protocols will be completed by the research team in collaboration with the staff implementing the QI protocol at each bridge organization and the CDS. The staff implementing the QI protocol will evaluate their own protocol in order to provide the staff with the tools and skills needed to conduct and assess future QI protocols (capacity building). Implementation fidelity will be assessed using similar metrics and methods as described for the QI intervention evaluation (see above description). During the planning process for the QI protocol, the research team staff will work with each organization to identify specific outcomes they want to focus on through their QI protocol. The QI protocols identified during this planning phase will be used to inform the data collected for both the process and outcome evaluation. Outcome measures will be based on data generated from weekly data files submitted to CMMI by each bridge organization as required per the Model terms and conditions of award. Weekly files are converted to CMS records and available through the bridge organization monthly monitoring report in the AHC Portal. We anticipate a period of 6 months of intervention data will be available for each site for comparative purposes. Each bridge organization will extract data from their monthly monitoring report for the previous 12 months, which will serve as the baseline data period. Data extracted for each bridge organization will vary per site and protocol based on the staff identified QI protocol and patient interviews but examples include: the unique number of beneficiaries who accepted navigation, the number of core needs resolved from navigation cases, and the number of closed navigation cases with no core needs met. Data for the intervention period (implementation of the QI protocol) will be extracted using the same report and measures. Descriptive statistics [mean, median, range, interquartile range (IQR)] will be calculated for each time period for all measures and compared across time using parametric or non-parametric statistics as appropriate.

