**Figure 2 F2:**
[figure not shown]
Quality improvement intervention.

Tasks will be replicated with five bridge organizations participating in the national AHC model.

Participating bridge organizations were chosen by an informal assessment of organization implementation needs, and interest in peer technical assistance through conversations between the research team and CMMI program officers. Potential bridge organizations were approached by the research team at the Annual AHC meeting attended by bridge organizations, CMMI and other CMS staff, federal agency partners, and CMS contractors. The research team then worked closely with potential bridge organizations and CMS program officers in follow-up meetings to determine interest and readiness to participate in SPAN. In Task 1, a mixed-method assessment will provide a baseline of the current AHC navigation implementation. Integrated findings from the baseline assessment will guide peer planning to introduce TA resources, to build relational elements and organizational capacity, and to establish priorities and visioning through stakeholder and planning meetings (Task 2). In Task 3, stakeholder meetings will be conducted to develop a quality improvement (QI) protocol and to update current AHC navigation implementation. Alongside the development and implementation of the QI intervention in the SPAN protocol, a mixed method, convergent parallel study will evaluate the impact of the peer planning approach and TA on implementation and navigation outcomes (Task 4). The study design will allow for accurate measurement of selected Consolidated Framework for Implementation Research (CFIR) constructs from Figure 1 while providing a complementary set of data for the overall national AHC Model without harming any desired measures for the larger national AHC evaluation or other outside evaluations. Study results will integrate findings across bridge organizations about AHC activities and navigation outcomes with the evaluation of the multi-level QI intervention and individual QI protocols.

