In the first stakeholder committee meeting, the research team will review the SPAN protocol and memorandums of understanding (MOUs), roles and responsibilities for committee members will be assigned, a communication plan will be created, and all committee members will agree on the goals for stakeholder meetings. In the second stakeholder meeting, baseline navigation data collection to identify if current navigation milestones are being met by bridge organizations and findings from the assessment (Task 1) will be discussed. The baseline navigation data will be collected from monthly monitoring reports each bridge organization must provide to CMMI. Before the meeting, the research team will present the process maps of the bridge organization's current site activities based on the assessment findings. Bridge organization and CDS stakeholders will review and provide feedback on the process maps during the meeting. During the first planning session meeting, the research team will review and make any additional modifications to the process map(s) created in the stakeholder meeting. Based on the assessment and process mapping, staff will align current implementation strategies with best practices based on the ERIC implementation strategies for multi-component interventions (34). In the second planning session meeting, an IM planning session will be held to focus on areas where QI could be helpful for the AHC site's current implementation approach and focus on prioritization of AHC implementation performance objectives and determinants. The aim of the second planning meeting is to identify between two and four modifiable determinants to be mapped to specific ERIC implementation strategies for QI. The staff will use these strategies to create the QI protocol, revised standard operating procedures (SOPs), implementation plan, navigation milestone plan, and other relevant QI documents at the third and fourth stakeholder meetings.

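### Each site chooses its outcomes after its baseline milestones are reviewed, and no common navigation measure is fixed for the before/after comparison that also feeds the overall evaluation

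*Protocol article*

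**What the plan says.** The SPAN Protocol section sets out the replication: "Tasks will be replicated with five bridge organizations participating in the national AHC model". The sites were not a random draw: "Participating bridge organizations were chosen by an informal assessment of organization implementation needs". The same section says what the study will deliver: "Study results will integrate findings across bridge organizations about AHC activities and navigation outcomes".

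Task 2 gives the order of events. Two of the four stakeholder meetings come before the planning session. The second of these covers "baseline navigation data collection to identify if current navigation milestones are being met by bridge organizations", together with the Task 1 findings. On the source it says: "The baseline navigation data will be collected from monthly monitoring reports each bridge organization must provide to CMMI". The planning session and the writing of the QI protocol follow.

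The section Evaluation of the QI Protocols says that each organization, with the research team, picks the outcomes for its own protocol during planning, and that "Data extracted for each bridge organization will vary per site and protocol based on the staff identified QI protocol and patient interviews". Three measures are given, as examples only: beneficiaries accepting navigation, core needs resolved, and cases closed with no core need met. Baseline is the previous 12 months of the monthly monitoring report. About 6 intervention months are expected, taken from the same report with the same measures. The periods are then compared by parametric or non-parametric statistics.

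The section Evaluation of the QI Intervention carries these results upward: "The outcomes from the QI protocols (described below) will also be used as metrics of success for the larger QI intervention".

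**The concern.** The study's aim is to improve navigation milestones through structured peer planning, tried at five sites. Tailoring the strategies to each site is the point of the intervention; tailoring the yardstick is a separate decision with a separate cost. If one site reports acceptance of navigation, another needs resolved and a third unsuccessful closures, no single before/after quantity describes what peer planning did across the five.

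The timing adds a second problem. The report that informs the choice of outcome also supplies the baseline against which that outcome is tested, and no concurrent comparison site is described. If a poor baseline value makes a measure more likely to be chosen, part of its later improvement is chance recovery, and the design cannot separate that from benefit.

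**Working it through.** **No planned figure to reproduce.** The article states no sample size, alpha, effect size or variance. The check has three parts.

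**1. Is any measure sure to be compared at all five sites?** Set side by side, the sections say that extraction varies by site, that the listed measures are examples, and that the site outcomes also serve the overall evaluation. None names a measure that every site must extract. The number of measures guaranteed in common is therefore zero, although all sites produce the same type of monthly report.

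**2. How large could regression to the mean be?**

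Inputs from the article: 12 baseline months, 6 intervention months, three example measures.

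Assumptions, not in the article:
- no true effect, and each measure scaled to a monthly SD of 1;
- measures independent of one another;
- lag-1 autocorrelation ρ of 0 or 0.5;
- SD τ of the true levels across measures of 0 or 1;
- the site picks the worst of three on the same 12-month mean.

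Let B be the 12-month baseline mean and F the 6-month follow-up mean. The expected worst of three lies 0.85 SD below average, so

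spurious gain = 0.85 × SD(B) × [1 − Cov(B,F)/Var(B)].

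- ρ = 0, τ = 0: Var(B) = 1/12, Cov = 0. Gain = 0.85 × 0.289 = 0.245. Simulated: 0.244.
- ρ = 0, τ = 1: Var(B) = 1 + 1/12 = 1.083, Cov = 1. Gain = 0.85 × 1.041 × (1 − 1/1.083) = 0.068. Simulated: 0.071.
- ρ = 0.5, τ = 0: Var(B) = (1/12)[1 + 2Σ(1 − k/12)0.5^k], k = 1 to 11, = 0.222. Cov = (Σ0.5^a, a = 0 to 11)(Σ0.5^j, j = 1 to 6)/72 = 2.00 × 0.984/72 = 0.027. Gain = 0.85 × 0.471 × (1 − 0.123) = 0.351. Simulated: 0.351.
- ρ = 0.5, τ = 1: Var(B) = 1.222, Cov = 1.027. Gain = 0.85 × 1.106 × (1 − 0.841) = 0.150. Simulated: 0.149.

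The simulation used 40,000 null runs per setting and a two-sample t-test at two-sided 0.05. The share of runs showing a false significant improvement was:

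| ρ, τ | Choice ignores baseline | Worst of three |
|---|---|---|
| 0, 0 | 2.5% | 5.5% |
| 0, 1 | 2.4% | 3.4% |
| 0.5, 0 | 11.2% | 20.8% |
| 0.5, 1 | 11.3% | 15.0% |

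The 11% in the lower rows comes from ignoring autocorrelation, not from selection. Only the rise above it belongs to this point.

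Two variations:
- If the choice rests on the last 3 baseline months only, the gain for three measures is 0.07 to 0.12 SD.
- If the choice ignores baseline, the mean change stays within ±0.01 SD in every setting.

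**3. What could five sites show on a common measure?** If all five improved, the sign test gives 0.5^5 = 0.031 one-sided and 0.0625 two-sided. A common measure makes a cross-site summary possible; it does not make it precise.

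**The case against.** The strongest reply is that outcome choice is not said to follow poor performance. The stated bases are the staff-identified QI protocol and patient interviews. The protocol itself is built from two to four modifiable determinants mapped to implementation strategies. Task 2 uses the baseline data to see whether milestones are met, and does not tell sites to target their worst figure. This stands, and it limits the regression point to a vulnerability. A reader might infer from the order of meetings that regression to the mean is bound to occur, but the text does not support that.

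It is also fair that the article does not say which months the meeting sees. CMMI approval and a readiness checklist fall between planning and the start, so part of the 12-month baseline may postdate the choice. The calculation on the same 12 months is therefore a scenario.

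A reader might further infer that decline in unchosen measures would go unnoticed. It need not: evaluators not directly involved in delivery also review the quarterly navigation milestone reports, although under process evaluation and with no statistic attached. Nor are the site outcomes the only basis for judgement, since document review and staff interviews contribute too.

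Finally, the article promises integration of findings in a mixed-method design, not a pooled estimate, and local tailoring is its declared logic. Narrative synthesis or a count of sites improving remains possible. What this leaves standing is that the article itself sets site-varying extraction and reuses the results for the overall judgement. That is a choice it makes, not a detail left to an analysis plan.

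**Conclusion.** The point holds in a limited form. Outcomes are chosen site by site after baseline milestones are reviewed, they also serve as success metrics for the overall QI intervention, and no quantitative navigation measure is sure to be compared before and after at all five sites. Direct pooling is not possible as written.

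The regression component is conditional: about 0.07 to 0.35 monthly SD under worst-of-three selection on the same 12 months with the assumed ρ and τ, and about zero if choice and baseline are unrelated. The documents give no basis for placing the study within that range.

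Two stronger readings should not be drawn. The first is that the sites can never be combined; the shared monthly report offers a common measure if one is named. The second is a large family-wise error obtained by counting three tests at each of five sites: the article states neither that number of tests nor an alpha, and independence between the example measures is doubtful.

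**What to change.** Before the second stakeholder meeting at any site, name a small core set from the monthly monitoring report. The three example measures would serve, expressed as rates where the report supplies a denominator. Extract the set for the 12 baseline and 6 intervention months at all five sites, whatever QI protocol each adopts.

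Name one core measure as the common navigation metric for the QI intervention. Report the five site estimates with intervals and a cross-site summary, and say plainly that five sites give an imprecise result. Keep the site-chosen outcomes as secondary, labelled as selected after baseline review.

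No new data collection is needed, only a few more fields from a report that every site already produces, and local tailoring of strategies is untouched. The drawback is that a core measure may be off-target for some sites and dilute the cross-site summary. The change also leaves the comparison uncontrolled and does not undo the need-based choice of sites, so both remain limitations to state.

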## Quality Improvement Approaches

Integrating QI approaches from lean manufacturing into the clinical healthcare space has provided positive and successful results (40). This kind of improvement is deemed “total quality management” and applies both qualitative and quantitative methods to ensure that healthcare processes produce outcomes which achieve desired results (41). *Lean Six Sigma* utilizes a 5-step method to assess if the desired quality of the healthcare outcome is achieved (41). These adapted steps are: define the goals; measure the current process; analyze to verify the relationships and causality of factors; improve the process based on the experimental analysis; and provide control to ensure the variances are corrected (41). This method combines the precision of replicating standards that can be grounded by the scientific method. *Lean Six Sigma* empowers staff with a defined framework for change that can improve work flows and meet identified strategic priorities. Collaboration is the hallmark of this methodology, and because it is process focused it does not interfere with the professional judgment of healthcare practitioners. Management buy-in is extremely important in the maintenance efforts to sustain these changes for the long-term and to empower other site staff and ensure long-term sustainability and success. We will use *Lean Six Sigma* as our QI method for the navigation process. As with traditional *Lean Six Sigma* initiatives, our aim is to improve performance, in our case navigation performance. We differ from the traditional *Lean Six Sigma* practice whereas waste and variation are removed, instead we seek to identify site specific solutions to reach common goals of improved AHC Model implementation and outcomes in the proposed Strengthening Peer AHC Navigation (SPAN) study protocol. The aims of the SPAN study protocol are to implement and evaluate a new multi-level quality improvement (QI) intervention to improve the Accountable Health Communities (AHC) Model implementation and navigation milestones through a structured peer planning and to provide successful technical assistance for the AHC Model.

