### Task 3 – Co-creation of a Quality Improvement (QI) Protocol for AHC Model Navigation Activities

Following peer planning, a third stakeholder meeting will be held with each bridge organization to develop a quality improvement (QI) protocol and to update QI documents for AHC Model implementation at the CDS. The QI protocol allows each bridge organization to demonstrate AHC navigation implementation achievement and determine short term impact on milestones. The protocol will build on activities and data collected in Tasks 1 and 2. The fourth stakeholder meeting will focus on key components of a QI protocol and completion of a written QI protocol. As shown in Table 2, the QI protocol will be completed using the Quality Improvement (QI) Bridge Organization Team Charter Template. The template was adapted from QI protocol charters developed by the Agency for Healthcare Research and Quality (AHRQ) Quality Indicators Toolkit (44), Institute for Healthcare Improvement (IHI) (45), and CMS Medicare Quality Assurance and Performance Improvement programs (46). The purpose of the template is to describe the stakeholder committee roles, QI protocol aims, scope and timeline, protocol implementation strategies, and change management strategies (e.g., how to measure QI protocol success). Upon review and approval by each bridge organization, the protocol will be sent to CMMI for review and approval. CMMI leadership and program officers will review the protocol to ensure there is no overlap with existing Model activities or budgetary fund allocation. Upon approval by CMMI, each bridge organization will complete the Quality Improvement Protocol Readiness Assessment Checklist outlined in Table 3 (47). Upon expressing readiness to implement the QI protocol, bridge organizations staff will be assigned to the new protocol, budgetary funds will be released to support implementation by the bridge organization and implementation will begin. A minimum of two additional stakeholder meetings will be held during QI protocol implementation to provide facilitation, support, and ongoing assistance to each bridge organization.

**Table 2 T2:** Quality improvement bridge organization team charter template.

Bridge Organization Name:
QI Protocol Aim:
Bridge Organization QI Protocol Sponsor:
Protocol Background:
QI Protocol Scope:
QI Protocol Implementation Strategies:
QI Protocol Change Management Strategies (take from planning meetings):
Estimated Date for Start and End of QI Protocol:

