
### Anticipated Challenges

While TA research has identified relational and content components, research is limited on TA within the context of relationship building in a peer planning approach. Identified challenges in peer planning include hesitation and lack of enthusiasm from stakeholders, lack of organizational leadership support, and limited capacity (e.g., time and resources) for AHC implementation (50). Strategies for overcoming these barriers include providing a venue (e.g., planning and stakeholder meetings) for stakeholders to discuss organizational successes, failures, and expectations. The meetings were created to engage stakeholders and develop capacity to implement the QI protocol. The roles and expectations of each stakeholder and organizational leader are clarified in these meetings in order to sustain support and engagement. Highlighting AHC successes and patient stories as models for organizational expectations can also assist in engaging organizational leaders. Prior to implementation, the assessment in Task 1 will identify current capacities and which capacities the TA provider should help each bridge organization build. With capacities identified, ongoing stakeholder meetings with TA provide support in implementing and evaluating the QI protocol.

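### The only before-after comparison described uses measures tied to each site's own QI protocol, so it cannot alone support a claim that navigation improved overall

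*Protocol article*

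**What the plan says.** The outcome data are described in the protocol article under Evaluation of the QI Protocols. During planning, "the research team staff will work with each organization to identify specific outcomes they want to focus on through their QI protocol". Extraction then follows that choice: "Data extracted for each bridge organization will vary per site and protocol based on the staff identified QI protocol and patient interviews". The source is the monthly monitoring report, built from weekly files that every site must submit. The baseline is the previous 12 months, and about 6 months of intervention data are anticipated. The intervention period uses the same report and the same measures. Each measure is summarised by period and compared over time with parametric or non-parametric methods.

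Three examples of measures are given: unique beneficiaries accepting navigation, core needs resolved, and cases closed with no core need met. They are illustrations, and none is required.

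Under Evaluation of the QI Intervention the article adds: "The outcomes from the QI protocols (described below) will also be used as metrics of success for the larger QI intervention". The study aim, under Quality Improvement Approaches, is wider: "to improve the Accountable Health Communities (AHC) Model implementation and navigation milestones". The Task 1 document review section notes that the funder's targets cover both screening and navigation.

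A second layer of evaluation exists. Evaluators not directly involved in delivery review the quarterly navigation milestone reports, and the introduction to Task 4 puts global navigation implementation in scope.

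**The concern.** The numerical evidence is narrower than the claim it is meant to support. Measures enter the before-after comparison because a site is trying to move them, or because patient interviews pointed to them. They then count towards the success of the whole intervention. Screening, referral and navigation follow one another, and a change at one step can be offset at another.

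Displacement is a reasonable worry in this setting. Anticipated Challenges lists "limited capacity (e.g., time and resources) for AHC implementation", and Task 3 says that once a site is ready, "bridge organizations staff will be assigned to the new protocol". If effort concentrates on the targeted step and a different step weakens, nothing in the described analysis requires that second step to be counted in either period. Site staff also take part in judging the result: "The staff implementing the QI protocol will evaluate their own protocol", in collaboration with the research team. At stake is whether a favourable table of chosen measures can be read as improved Model implementation.

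**Working it through.** The article gives no sample size, effect size, error rate or success threshold, so there is no figure of its own to reproduce. The check has two parts: setting the sections side by side, and an assumed illustration of size.

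**Sections side by side**

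| Question | What the article fixes | Where |
|---|---|---|
| What should improve? | Model implementation and navigation milestones | Quality Improvement Approaches |
| Which measures are compared numerically? | Those tied to each site's QI protocol and patient interviews | Evaluation of the QI Protocols |
| Are any measures common to all five sites? | None stated | Evaluation of the QI Protocols |
| What feeds overall success? | The QI protocol outcomes, among other evidence | Evaluation of the QI Intervention |
| How are milestone reports used? | Reviewed as documents in the process evaluation; no numerical comparison described | Evaluation of the QI Intervention |

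A measure that a site does not select is therefore not required in either period, and the one source that might show the overall picture has no stated before-after analysis.

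**Illustration of size (assumed values)**

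Total needs resolved = number accepting navigation × needs resolved per accepted case.

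Suppose acceptances rise by a fraction g and needs resolved per case fall by a fraction x. The total is unchanged when (1 + g)(1 − x) = 1, so x = g/(1 + g).

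- g = 0.10: x = 0.10/1.10 = 0.091, a fall of about 9%.
- g = 0.20: x = 0.20/1.20 = 0.167, a fall of about 17%.
- g = 0.30: x = 0.30/1.30 = 0.231, a fall of about 23%.

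A site that chose acceptances as its measure and did not also extract needs resolved would show a 20% gain with no change in total needs resolved.

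**Which losses stay hidden**

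Direction matters, because the article's examples are counts. A count already absorbs losses at earlier steps. If the acceptance rate rises 10% and the number screened falls 9.1%, the number accepting changes by 1.10 × 0.909 = 1.00, so no gain appears. For count measures, then, the unseen loss must lie downstream of the chosen step or in a parallel activity. A fall upstream would be concealed only if a site chose a conditional rate, and none of the three examples is one.

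**The case against.** The case against is substantial, and several stronger readings that a reader might infer do not hold.

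- **Losses would go unseen.** Not supported. Separate evaluators have the quarterly milestone reports before them, the Discussion names those reports again as a data source, and baseline navigation data are set against milestones at the second stakeholder meeting. A fall in milestone performance could be noticed. What stands is that no quantitative comparison of those reports is described, and their coverage of screening is not stated.
- **Staff are taken off other work.** Not stated. They are assigned to the QI protocol, which itself concerns navigation, and funds are released to support it. The funder also reviews each protocol for overlap with existing activities. Limited capacity is listed as a general challenge of peer planning, with mitigation strategies. Displacement remains a risk to be checked.
- **Sites alone pick flattering measures.** Too strong. The research team helps choose, patient interviews shape extraction, and one example measure is unfavourable in direction. None of this makes an untargeted measure mandatory.
- **A success rule is being abused.** The article has no threshold for calling a site improved, and the QI protocol outcomes are one success metric beside interviews and document review.

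It can also be said that a condensed article leaves site measures to the site charters. That excuses not listing each site's measures. It does not answer the rule the article does state, which lets extraction vary by site and then carries the results up to the whole intervention.

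**Conclusion.** The point holds in a limited form and is worth correcting. The only quantitative before-after comparison described covers measures that follow from what each site targets, while the aim and the success claim are general. A favourable result on those measures does not by itself show that the Model's navigation work improved overall.

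The size cannot be derived from the article. The offset of 17% against a 20% gain is an illustration, and it assumes that the chosen measure is acceptances and that needs resolved is not also extracted. A site that selected both would see the loss. The conclusion also assumes that the document review of milestone reports involves no numerical comparison beyond what is described. The article does not show that displacement will happen or that it would escape every evaluator.

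**What to change.** Under Evaluation of the QI Protocols, require all five sites to extract a fixed set of screening and navigation measures from the monthly monitoring report, including those the site does not target. Cover both the 12-month baseline and the anticipated 6-month intervention period. Fix the set before the QI protocol starts, limited to what the report contains, since the article does not list its contents in full. Give these measures the same before-after summaries as the site-chosen ones, show the two side by side, and word any conclusion about overall Model improvement in light of both.

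Do not add a rule that any fall on an untargeted measure disqualifies a site. With three independent measures and no true change, each equally likely to rise or fall, at least one falls with probability 1 − 0.5³ = 0.875. Such a rule would reject most unaffected sites by chance.

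The cost is slightly more extraction from a report the sites already use. The downside is that some sites' results may look less favourable.
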